| 
 
5-point Likert responses to items on confidence and trust Describe confidence and trust in results among women who have completed a kit self-reported kit engagement among women who did not complete a kit
 
                      | Self-reported opening of the kit; self-reported attempt to use the kit                                                                                                            | Descriptive data on yes/no responses to two items assessing opening of the kit and attempt to use it.                                                                                                                                                                                                                                                                                                                                                                                                        |
| Exploratory Objectives                                                                                                                                                                                                                                                             | Exploratory endpoints                                                                                                                                                             |                                                                                                                                                                                                                                                                                                                                                                                                                                                                                                              |

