### **4.5 Questionnaire-based sub-study**

A cross-sectional, descriptive questionnaire-based sub-study will be nested within the feasibility trial. The purpose will be to understand more about the women who take up the offer of a self-sampling kit, and about their previous barriers to participation. A short questionnaire will be included in the self-sampling kits which are posted or handed out to women. The focus of the sub-study will be on women who do return a kit, but questionnaires will be mailed/handed to all women as part of the YouScreen kit and we will include a small number of questions designed to understand why some women do not return the kit – albeit anticipating a low response rate in this group. In this brief questionnaire sub-study, we will use the Precaution Adoption Process Model (PAPM) (26) as a theoretical framework and will draw on [name] previous work to explore previous barriers to participation.(27-30)

In the patient information booklet, women will be invited to complete the questionnaire and mail it to KCL by freepost. Questionnaires will be a single page of A4, folded and sealed (self-seal), with pre-paid postage and address printed on the reverse side. We may include a link for women to complete the questionnaire online instead of completing and returning by post.

The questionnaire will be pre-printed with the kit ID number to allow linkage to information about the mode of kit offer, return of self-sample, the woman's cervical screening history, HPV result and (if HPV positive) attendance for follow-up, as well as basic demographic information not collected as part of the questionnaire e.g. LSOA (Lower Layer Super Output Area).

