**Figure 1 Timeline of call/recall letters and study direct mail-out of kits**

[figure not shown]

The NHAIS extract will include the women's:

- Full name
- Date of Birth
- Address including postcode
- NHS number
- GP Practice Code

These are the minimum fields required to ensure that kits can be sent to the correct women's homes identified at the lab and that the results can be accurately reported to the correct women and correct GP practice.

NHS Digital will make the list of eligible women from current participating GP Practices in NHAIS available to the Cervical Screening Administration Service (CSAS) who are responsible for sending invitations and reminders for the call/recall Cervical Screening Programme in England (see Figure 2 for further details). CSAS will then send the list to a commercial print company (contracted by UCL and/or KCL) with the appropriate level of information governance standards to securely handle NHS data (i.e. with International Organisation for Standards (ISO) accreditations and Information Governance (IG) approved on the NHS IG tool kit, their Data Security and Protection Toolkit will be compliant with NHS Digital Data Security and Protection regulations).

The print company will send a pre-notification letter to women (on behalf of the GP practices and the Cervical Screening Programme) informing them that they are overdue cervical screening and that a self-sampling kit will be posted to them. It has been hypothesised that sending a pre-notification letter enhances self-sampling uptake. Within 1-2 weeks of sending the letter, the print company will send women a self-sampling kit along with an invitation letter.

GP endorsement may be included on the pre-notification and/or invitation letters as this has been shown to increase participation in colorectal screening (and would be cost neutral).

Self-sampling kits in the mail-out arm will comprise:

- A CE-marked dry flocked swab (552C.80 Copan FLOQswab™) in a tube with a re-sealable lid
- Pictorial and written instructions for self-collecting the vaginal sample
- A UN3373-compliant freepost envelope (padded or polybag) or box that is pre-addressed to the laboratory

- A patient information booklet
- A specimen bag
- A lab request/consent form
- A questionnaire (questionnaire-based sub-study)

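### The kit-opening question for non-completers travels inside the kit, so it will read close to 100% yes and cannot estimate how many of them opened it

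*Protocol*

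**What the plan says.** Among the secondary objectives, protocol section 3.2 lists "self-reported kit engagement among women who did not complete a kit". The endpoint is "Self-reported opening of the kit; self-reported attempt to use the kit" and the measure is "Descriptive data on yes/no responses to two items assessing opening of the kit and attempt to use it".

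Section 4.5 fixes the delivery route: "A short questionnaire will be included in the self-sampling kits which are posted or handed out to women". Women who do not return a sample are reached in the same way: "questionnaires will be mailed/handed to all women as part of the YouScreen kit". On how women are asked to take part, it says: "In the patient information booklet, women will be invited to complete the questionnaire and mail it to KCL by freepost". The kit-contents lists in sections 7.2.1 (mail-out) and 7.2.2 (opportunistic) each include both the questionnaire and the booklet.

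The only other route named is optional: "We may include a link for women to complete the questionnaire online instead of completing and returning by post". The protocol does not say where such a link would appear. It describes no separate questionnaire mailing to women who have not returned a sample.

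Sections 4.5 and 9.1.3 do warn of low response from non-completers, and section 9.1.3 calls statistical comparison with completers inappropriate. Neither says that reaching the questionnaire depends on opening the kit.

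**The concern.** A woman who leaves the kit unopened does not see the question about whether she opened it. A no is therefore largely excluded by the delivery route, and a high share of yes answers would say nothing about behaviour.

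Section 4.5 says the non-completer questions are there to learn why some women do not return the kit, and section 1 notes that attrition after direct mail-out can be high. Never opening the kit and opening it without sampling are different failures and would point to different changes in a roll-out. The item cannot separate them, and a figure near 100% could be reported as if it were a result. No later analysis can repair this, because the women concerned were never asked.

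**Working it through.** **1. The plan's own sub-study figures.** Section 9.1.3 and Table 3 give 31,000 questionnaires sent, response rates of 90% (completers) and 10% (non-completers), and returns of 5,580 and 2,480. The completion share is not stated; back-solving gives 20%:
- completers: 31,000 × 0.20 = 6,200, and 6,200 × 0.90 = 5,580
- non-completers: 31,000 × 0.80 = 24,800, and 24,800 × 0.10 = 2,480
- total: 5,580 + 2,480 = 8,060

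All three figures reproduce exactly.

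**2. The number of non-completers from the main sample-size text.**
- mail-out (section 9.1.1): 19,000 − 2,800 = 16,200
- opportunistic (section 9.1.2): 12,000 − 8,500 = 3,500
- total: 16,200 + 3,500 = 19,700

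This differs from the 24,800 behind Table 3, because 11,300 / 31,000 is 36.5% completion rather than 20%. Both figures are carried here, and the argument depends on neither.

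**3. What the opening item would show.** Let π be the true share of non-completers who opened the kit, and k the response rate of non-openers divided by that of openers. Then

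observed share opened = π / (π + (1 − π) × k).

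The protocol gives neither quantity, so the ranges below are assumptions.

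| k | π = 20% | π = 50% | π = 80% |
|---|---|---|---|
| 0 (in-kit route only) | 100% | 100% | 100% |
| 0.01 | 96.2% | 99.0% | 99.8% |
| 0.05 | 83.3% | 95.2% | 98.8% |
| 0.10 | 71.4% | 90.9% | 97.6% |
| 1 (route independent of opening) | 20% | 50% | 80% |

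For example, at π = 0.5 and k = 0.05: 0.5 / (0.5 + 0.5 × 0.05) = 0.952. The in-kit route alone is k = 0.

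**4. Apparent precision.** If all n responding non-completers say yes, the exact 97.5% lower bound is 0.025^(1/n). This is 99.85% for n = 2,480. For n = 248 (a 1% response from 24,800; section 9.1.3 reports just under 1% in an earlier study) it is 98.52%. Such an interval would look precise and would carry no information about π.

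**5. The attempted-use item.** This can vary among respondents. If 30% said yes (an assumed value), the 95% half-width is 1.96 × √(0.3 × 0.7 / n): 1.8 points at n = 2,480 and 5.7 points at n = 248. That describes responding openers only. For all non-completers, letting every non-respondent be a no or a yes gives:
- 10% response: from 0.10 × 0.30 = 3% to 3% + 90% = 93%
- 1% response: from 0.01 × 0.30 = 0.3% to 0.3% + 99% = 99.3%

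**The case against.** A reader might infer that the whole kit-engagement endpoint is lost. The protocol does not support that. There are two items, and attempted use is not fixed by where the questionnaire is packed.

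A reader might also infer that the opening item can only ever be answered yes. That is too strong:
- The item wording is not shown, and opening could refer to an inner component.
- The optional online link might sit outside the kit.
- Section 7.3 puts translations of the booklet on a website.
- For opportunistic kits, staff write on the tube label at hand-over (section 7.2.2) and women may sample at the practice, so who opened the kit is unclear.

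These are reasons to say close to 100% rather than exactly 100%. None is a committed route to women who leave the packet unopened, and the unclear meaning of opening is itself a weakness of the item.

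A third tempting step is to put a size on the overstatement: 100 minus an assumed share for opening, or division by the share opened for attempted use. The first has no source in the protocol. The second also needs responding openers to resemble all openers, which nothing supports at the response rates expected.

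Finally, it can be said that the protocol already discloses the weakness and promises only description. The disclosure concerns low response, which costs precision and can bias. It does not cover exclusion by delivery route: even if everyone who saw the item replied, the answer would still be near 100%. The modest descriptive purpose does limit the consequences, and that part of the objection stands.

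**Conclusion.** The opening item is uninformative by design. Under the delivery route the protocol commits to, it will read close to 100% yes whatever the true share. It can neither estimate the share of non-completers who opened the kit nor separate never opened from opened but not sampled. Attempted use remains describable, but only among non-completers who opened the kit and replied.

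This rests on the questionnaire and its invitation reaching women essentially only through the kit, and on opening meaning the kit itself. A sizeable route outside the kit would weaken it, as the table shows at k = 0.10. The opening shares and response ratios are illustrative.

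The point is minor. It affects one of two descriptive items in a nested sub-study and touches no primary endpoint or sample size.

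**What to change.** In section 3.2, delete opening of the kit as an endpoint and restate the measure as attempted use among responding non-completers who opened the kit. This costs one line and changes no procedure.

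If opening is still wanted, ask it by a route that does not depend on opening the packet, such as a link with the kit ID printed on the outer packaging or sent separately, and define what counts as opened in each pathway. The invitation letter is not a safe vehicle: section 7.2.1 sends it along with the kit, possibly in the same packet. The cost is a print or mailing change. Low response among non-openers would remain a limitation and should be stated beside the result.

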## 1 BACKGROUND

Cervical screening coverage in England has been falling and is currently at a 20 year low.(1) London consistently has the lowest cervical screening coverage nationally - 64.7% versus 71.4% across England in 2018.(1) Patches in North East (NE) and North Central (NCL) London are amongst the worst performers (age appropriate coverage in Camden CCG 54.6%, Tower Hamlets CCG 60.9% in 2017/18).(2) The North Central and East London Cancer Alliance (NCELCA) commissioned by NHS England to drive local change in the quality of cancer services such as screening, to improve cancer outcomes and patient experience. NCELCA are extremely keen to tackle the issue of falling coverage in their patches.

Currently the most promising solution to this longstanding issue is to offer self-sampling for HPV testing to women who have not attended for screening (i.e. non-attenders). Common barriers to cervical screening include fear or dislike of the pelvic examination, embarrassment, difficulty getting appointments or being too busy.(3-5) Self-sampling addresses most screening barriers enabling women to take a sample themselves, in private and at a time and place of their choosing. There is also robust evidence that offering HPV self-sampling to non-attenders can increase screening uptake, on average by 10%.(6, 7) However, uptake rates are highly variable between studies (6.4%-34%).(6, 8, 9)

In terms of clinical test performance, evidence from an international meta-analysis (including 56 accuracy studies) reported that HPV testing on self-samples are similarly accurate to clinician samples for cervical screening (i.e. for detecting high-grade cervical disease) when using an assay based on polymerase chain reaction.(6, 10, 11) A large non-inferiority trial (the IMPROVE study) that was nested within the Dutch Cervical screening programme showed that primary HPV testing on self-samples in an organised screening setting was non-inferior to clinician-taken HPV samples.(10) In addition, long term (5 year) follow data from a population-based self-sampling study in Scotland show that the risk of CIN2+ and CIN3+ in women with an HPV negative self-sample is extremely very low (0.6% and 0.2%, respectively).(12)

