| To examine in more detail the opportunistic offer of self-sampling in GP primary care (if data allow)                                                                                                                                                                              | 
Response rates of eligible women offered kits in GP primary care
 
Reasons for declining kits
 
Kit offer and response to offer by health care professional type
 | 
The number of women who (i) accept a kit or (ii) decline a kit as a % of total number of eligible women offered kits opportunistically in GP primary care (GP record data)
 
Aggregated data on the main reasons for declining kits (GP records): number of women with each key reason provided as a % of all women recorded as declining kits (GP record data)
 
Number of kits (i) offered and (ii) accepted by health care professional type as a % of all kits offered (GP record data)
 |
| To assess any potential “nudge” effect towards the uptake of conventional screening associated with offering self-sampling                                                                                                                                                         | Uptake of conventional screening within 3 months of offer of self-sampling                                                                                                        | 
At participating GP practices:
 
Number of women who attend for conventional screening (and do not return a self-sample) within 3 months of the date of 15-month mailout pre-notification letter is sent (NHAIS &
                                                                                                                                                                                                                                                                            |

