|                                                                                                                                                      |                                                                                                                                                                                |                                                                                                                                                                                                                                                                                                                                                                                                                   |
|------------------------------------------------------------------------------------------------------------------------------------------------------|--------------------------------------------------------------------------------------------------------------------------------------------------------------------------------|-------------------------------------------------------------------------------------------------------------------------------------------------------------------------------------------------------------------------------------------------------------------------------------------------------------------------------------------------------------------------------------------------------------------|
|                                                                                                                                                      |                                                                                                                                                                                | 
CFH Docmail data) as a % of all women sent 15-month mailout pre-notification letter
 
Vs
 
Number of women who attend for conventional screening in months 12-14 as a % of all women who reach the 12-month anniversary of their last test due date without being screened (NHAIS data)
                                                                                                          |

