#### 4.1.2 Historical cohort “control” data

Historical (retrospective) data will be collected using a pre-written search of the electronic patient record system at participating GP practices for the 12 month period before the trial start. Women who are at least 6m overdue screening or who reached the 15m anniversary on a census date of 12 months before the trial start (“control” data) will be identified. Of these women, we will assess the proportion that were screened in the following 12 month period. This will be collected at or close to trial start (“entry”) for each GP practice and will allow us to more robustly assess the impact of offering self-sampling.

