### 9.1.1 Direct Mail-out

Assuming 106 GP practices recruit women for an average of 9 months (GP practices will recruit for a minimum of 6 months and a maximum of 12 months given that study set-up at each practice will be staggered over a 6 month period) and 20 women reach the 15 month anniversary at each practice each month, approximately 19,000 women will be sent kits during the trial. Table 2 below provides the expected 95% confidence intervals for various uptake levels over an average of 9 months recruitment period. We have estimated that 15% of women who receive a kit via direct mail-out will return a self-sample (i.e. ~2,800 women will return a self-sample over an average of 9m).

**Table 2 Expected 95% confidence intervals for different proportions of women who return a self-sample based on 106 GP practices over a 9-month average recruitment period**

| Uptake among those offered kits | 95%CI     |
|---------------------------------|-----------|
| 10%                             | 9.6-10.4  |
| 15%                             | 14.5-15.5 |
| 20%                             | 19.4-20.6 |
| 30%                             | 29.3-30.7 |

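### The exploratory nudge measure compares women at 15 months overdue with women at 12 months, so it is confounded by time overdue and mixes substitution with any nudge

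*Protocol*

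**What the plan says.** The objective in section 3.2 is "To assess any potential “nudge” effect towards the uptake of conventional screening associated with offering self-sampling". The measure is fixed in the same table, for participating practices.

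- **Letter group, numerator:** "attend for conventional screening (and do not return a self-sample) within 3 months of the date of 15-month mailout pre-notification letter".
- **Letter group, denominator:** "as a % of all women sent 15-month mailout pre-notification letter". Self-samplers are kept in.
- **Comparator:** "Number of women who attend for conventional screening in months 12-14 as a % of all women who reach the 12-month anniversary"; that is, among women 12 months overdue and still unscreened. No self-sample exclusion is stated.

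Four other sections bear on this:

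- Section 7.2.1 sends the mail-out only to women who reach 15 months unscreened, and places that point roughly midway between routine letters.
- Sections 4 and 7.2.2 have every participating practice offer opportunistic kits to women at least 6 months overdue.
- Section 7.5.2 sends HPV-positive self-samplers for a conventional test.
- Section 4.1.2 plans a historical control: "Women who are at least 6m overdue screening or who reached the 15m anniversary on a census date" 12 months before trial start, followed for 12 months. The nudge measure does not use it.

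**The concern.** A nudge measure should show no difference when the letter and kit leave conventional attendance unchanged. This one need not, for three reasons.

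1. **Time overdue.** Anyone screened in months 12-14 counts as a comparator success and can never enter the letter group. The letter group is what remains of the comparator population, seen later and at a different distance from the routine letters.
2. **Substitution.** A woman who would have attended but self-samples instead disappears from the letter-group numerator and stays in the denominator. A fall for this reason is a different finding from the absence of a nudge, and the single percentage cannot separate them.
3. **Comparator exposure.** Women in months 12-14 at trial practices may already be offered kits, so they are not an unexposed control.

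The practical risk is that a real nudge is hidden, or that deterrence is reported where there is none, in a trial meant to inform wider roll-out.

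**Working it through.** **The plan's own figures.** The protocol gives no figure for the nudge measure. Its mail-out figures reproduce: 106 practices x 9 months x 20 women = 19,080 (stated as about 19,000), and 0.15 x 19,080 = 2,862 returns (stated as about 2,800).

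**Inputs**

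- u, mail-out uptake: 15% (section 9.1.1); 6.4% to 34% in earlier studies (section 1).
- p, conventional attendance in months 12-14: not given. Assumed 2%, 5% or 10%.
- r, underlying attendance in the 3 months after month 15 divided by p: not given. Assumed 0.8 to 1.3.
- k, self-sampling among would-be attenders relative to overall uptake: not given. Taken from 0 (no self-sampler would have attended) to 1 (average rate).

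**Formula.** With no nudge, and ignoring kits in the comparator window:

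letter-group rate = p x r x (1 - k x u); ratio to comparator = r x (1 - k x u).

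**Exclusion alone (r = 1)**

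| u | k = 0 | k = 0.5 | k = 1 |
|---|---|---|---|
| 6.4% | 1.00 | 0.968 | 0.936 |
| 15% | 1.00 | 0.925 | 0.85 |
| 34% | 1.00 | 0.83 | 0.66 |

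At u = 15% and k = 1 this is 1.70% v 2.00%, 4.25% v 5.00% or 8.50% v 10.0%, depending on p. If would-be attenders self-sampled at twice the average rate, the ratio would be 1 - 2 x 0.15 = 0.70.

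**Adding timing (u = 15%, k = 1).** The ratio is r x 0.85: 0.68 at r = 0.8, 0.765 at r = 0.9, 0.935 at r = 1.1 and 1.105 at r = 1.3. It passes 1 at r = 1/0.85 = 1.18.

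**Window length.** If months 12-14 is read as the two months between those anniversaries, then a constant monthly rate gives 1.5 x 0.85 = 1.275, an apparent positive nudge.

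**Opportunistic kits.** If they draw would-be attenders out of the comparator numerator, the comparator rate falls and the ratio rises. The protocol gives no figure for this.

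**Size against sampling error.** Assuming 19,080 women per group, no clustering, r = 1 and k = 1, a two-sided 5% test would call the difference significant about 94% of the time at p = 5% and 58% at p = 2%. No such test is planned. The point is only that large numbers do not remove the shift.

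**If the exclusion were deleted.** HPV-positive follow-up tests would enter the numerator. With about 82% attending follow-up (section 7.5.2) and an assumed positivity of 8% to 18%, that adds up to 0.15 x 0.08 x 0.82 = 1.0 to 0.15 x 0.18 x 0.82 = 2.2 percentage points if all of it fell within 3 months.

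**The case against.** The strongest reply has four parts.

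- **The exclusion has a purpose.** It stops HPV-positive follow-up tests from counting as a nudge. This stands, and simply deleting the exclusion would be no repair.
- **Substitution is real.** If women self-sample instead of attending, the offer did reduce conventional attendance, and a proportion of all women sent the letter is a legitimate net effect. This stands too. However, the stated objective is a nudge towards conventional screening, and one net figure cannot show how much of a fall is substitution. Section 7.8.2.1 itself leaves open whether self-samplers would have come anyway.
- **The direction is not established.** A reader might infer that the measure must show a negative nudge when none exists. The documents do not support that. They give no monthly attendance rates, the cost of the exclusion may be zero, the two windows sit differently in the letter cycle, and opportunistic kits can lower the comparator rate.
- **The endpoint is minor.** It is exploratory, section 9.1 says the trial is not designed to compare two arms, and section 7.8.2.1 plans a further look at the nudge. This limits the importance of the point but does not justify a comparator taken at a different overdue time when a matched one is already planned.

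**Conclusion.** The measure does not isolate a nudge. The timing fault follows from the definitions alone: the letter group are the women left over from the comparator window, and comparator women may be offered kits. At 15% uptake the exclusion lowers the letter-group rate by between 0% and 15% relative, provided would-be attenders self-sample at no more than the average rate. At the average rate the loss is 6.4% to 34% over the cited uptake range. Part of it is genuine substitution.

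The net bias is probably towards a negative nudge, because the women most ready to attend leave before month 15. That is a judgement: the sign depends on attendance rates the protocol does not give, and reverses at 15% uptake with k = 1 once attendance after month 15 exceeds that in months 12-14 by about 18%. The point is worth correcting. It leaves the primary endpoints untouched.

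**What to change.** 1. Make the main comparator women who reached the 15-month anniversary before kits were offered: the section 4.1.2 cohort, or preferably the equivalent NHAIS women before practice start. Count both groups over the same 3 months from the same starting point, apply the mail-out's exclusions to both, and use the same data source where possible. Keep months 12-14 as supportive, with its length in months stated.
2. Over the single denominator of all women reaching 15 months, report side by side: conventional screening first (before any self-sample), self-sample, and any screening. Do not count HPV-positive follow-up tests as a nudge. Relabelling self-sample return as a competing event would not be enough alone, since it nearly reproduces the present percentage. Substitution becomes visible only when the three figures stand together.

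**Cost.** Protocol wording, plus test dates within the historical extract so that its 12-month follow-up can be cut at 3 months. The comparison then carries a calendar-year difference and, if the section 4.1.2 cohort is used, a GP-record versus NHAIS difference; section 10.4.1 calls GP records the less accurate source. The cohort may also be small. If one census date captures one month's women, it holds about 20 x 106 = 2,120. At an assumed 5% in both groups, the 95% half-width of the difference is then 1.96 x sqrt(0.0475/2,120 + 0.0475/19,080) = 0.98 points, so several census months would be better.
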